### Study outcomes

The primary outcome will be judged by a binary composite indicator. Children classified as “favourable outcome” fulfil all of the following criteria: alive, not acutely malnourished per the anthropometric definition applied at inclusion (MUAC > 125mm and WHZ > − 3, and no oedema) and not having an additional episode of AM throughout the 6-month observation period. This outcome is measured at 6 months after randomisation. All other children are classified as “unfavourable outcome”.

The main secondary outcome #1 will be determined among children who meet the current WHO definition of SAM at inclusion (MUAC < 115 mm or WHZ < − 3 or oedema +, ++). The main secondary outcome #2 will be determined among children admitted with a MUAC < 115mm or oedema (+, ++). For these two subgroups, recovery is defined in each arm by a 4-week minimum duration of treatment, an axillary temperature < 37.5 °C, and an absence of bipedal oedema and a MUAC ≥ 125 mm for two consecutive weeks. This outcome is measured throughout the 6 months post-randomisation, meaning a child will be considered as recovered if he reaches these criteria during the 6-month follow-up in outpatient or village visits. Additional secondary outcomes are listed in Table 1.

**Table 1 Tab1:** Primary and secondary outcomes in the OptiMA Niger trial

	Measurement variable	Method of aggregation	Time point

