### Eligibility criteria

Children aged 6–59 months, living for more than 6 months in one of the four health areas, and meeting at least one of the three following AM criteria are eligible for inclusion in the trial: MUAC < 125 mm and/or bilateral pitting oedema (+/++) and/or WHZ < − 3. Children with a medical complication requiring hospitalisation; no appetite; oedema grade +++; with a known allergy to milk, peanuts, or RUTFs; with a chronic disease (such as sickle cell anaemia, trisomy 21, congenital heart disease, neurological disease); or children already enrolled in a malnutrition programme are excluded from the trial.

Two categories of children are included in the trial but not eligible for randomisation for ethical concerns. First, children with WHZ < − 3 and MUAC ≥ 125 mm without oedema are systematically included in the control arm, as they are not eligible for RUTF regarding the definition of wasting in neither OptiMA nor ComPAS strategies. Second, children with a sibling already enrolled in the trial are systematically allocated to the study arm of the index sibling. Ultimately, children with MUAC < 125 mm and/or bilateral oedema and with no sibling already included in the trial are individually randomised.

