**Main secondary**			
Recovery	Composite: absence of bipedal oedema and a MUAC > 125 mm for two consecutive weeks, a 4-week minimum duration of RUTF treatment, and a good clinical health (without fever)	Proportion	Throughout the 6-month follow-up period
**Secondary**^a^			
Cost-effectiveness	Incremental cost-effectiveness ratio (ICER)	Ratio	Throughout the 6-month follow-up period
Consumption of RUTF per children with a favourable outcome	Sachets of RUTF consumed	Mean	6-month post-inclusion
Consumption of RUTF per recovered children	Sachets of RUTF consumed	Mean	End of RUTF treatment initiated at inclusion
Average daily weight gain in SAM children recovered	g/kg/day	Daily	End of RUTF treatment initiated at inclusion
Average daily MUAC gain in SAM children recovered	mm/day	Daily	End of RUTF treatment initiated at inclusion
Hospitalisation	Children with at least one episode of hospitalisation	Proportion	Throughout the 6-month follow-up period
Relapse to a new episode	Children with MUAC < 125 or WHZ < − 3 *Z*-score or oedema after RUTF treatment	Proportion	After recovering from the first episode of acute malnutrition
Non-response	Children who did not reach the recovery criteria	Proportion	16 weeks after inclusion
WaST	Children associated with severe and moderate stunting with acute malnutrition	Proportion	Throughout the 6-month follow-up period

^a^All the secondary outcomes will be analysed for the overall population (MUAC < 125 mm or WHZ < − 3 or oedema) and for the secondary populations (SAM WHO and MUAC < 115 mm or oedema)

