### Randomisation

Randomisation was performed using specially developed software, containing lists prepared in advance by an independent statistician, and inaccessible to trial staff. The randomisation is done in blocks (block size is kept confidential) and stratified at the study site by the severity of AM according to the following criteria: MUAC < 115 mm or oedema, MUAC > 115 mm and WHZ < − 3, and MUAC between 115 and 124 and WHZ > − 3 without oedema. This stratification allows for the recruitment of comparable groups of SAM WHO, MUAC < 115 mm, and non-SAM children and for simultaneous randomisation at the four sites. Once the randomisation was decided by the investigator on the basis of the verification of the eligibility criteria, they interrogated this software, which assigned the code and the corresponding treatment. This software assigns a treatment arm by sequentially drawing from this list each time a randomisation procedure is completed. After the children were assigned to an arm by the software, the trial and clinic staff were informed of the assigned treatment and therefore became unblinded. Once the sample size for the primary objective will be reached, only SAM WHO and then MUAC < 115 mm or oedema children will continue to be enrolled and randomised until the sample size required for the two main secondary objectives will be attained.

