**Assessments**				
Nutritional and medical assessment	x	x	x	x
Hospitalisation if required		x	x	x
Adverse event		x	x	x

^1^Minimum of 4 weeks of RUTF supplementation and a maximum of 16 weeks for the first episode of AM and if relapse

^2^After discharge from the outpatient visit or for children not eligible for supplementation (standard arm aged 24–59 months with a MUAC 115–124 mm and WHZ > − 3 and no oedema)

^3^At the discharge outpatient visit

Failure to reach recovery criteria is defined after 16 weeks in the programme, then children are discharged from OTF as non-responders and consulted once a month at home until they reach the 6-month post-inclusion. For each non-responder discharged with a MUAC < 115 mm, a medical committee meets to decide on the medical follow-up of the child in the trial. Defaulters are defined as a child absent for 3 consecutive visits. CHWs trace children who are absent to motivate caretakers to return to the health facilities. If caretaker refuse to return to the health centre, the child is followed up once a month at home until the 6-month post inclusion period. When caretakers refuse the follow-up at home, the exit status of children is declared “confirmed defaulter” when the vital status is known and “lost to follow-up” when the vital status is unknown.

Children are discharged from outpatient treatment according to the anthropometric exit criteria of their allocation arm. In standard protocol, children need to achieve a MUAC ≥ 125 mm and a WHZ ≥ − 2 without oedema for two consecutive weeks while in OptiMA and ComPAS strategies, children will be discharged if they reach a MUAC ≥ 125 mm without oedema for two consecutive weeks. For each arm, all children will have to participate a minimum of 4 weeks in the programme with good clinical health (absence of fever) to be discharged from the OTF.

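### The primary outcome's MUAC and WHZ cut-offs are not the complement of the inclusion definition they claim to restate, and Table 1 and the text disagree on whether 125 mm counts as recovered

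*Protocol article*

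**What the plan says.** Primary outcome (Study outcomes): the child must be alive, free of any further episode, and not malnourished "per the anthropometric definition applied at inclusion (MUAC > 125mm and WHZ" above −3, without oedema. The timing is fixed: "This outcome is measured at 6 months after randomisation". Everyone else falls in the residual class: "All other children are classified as “unfavourable outcome". The Table 1 row for the same outcome refers to the inclusion definition and gives no cut-off.

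Inclusion (Eligibility criteria): a child qualifies with "MUAC < 125 mm and/or bilateral pitting oedema" and/or WHZ below −3.

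Recovery, the main secondary outcome, appears with two signs:
- Study outcomes text: "an absence of bipedal oedema and a MUAC ≥ 125 mm for two consecutive weeks". The abstract and the Table 2 definitions for all three arms also use ≥ 125 mm.
- Table 1: "absence of bipedal oedema and a MUAC > 125 mm for two consecutive weeks".

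Discharge (Follow-up) uses ≥ 125 mm in every arm. In the standard arm "children need to achieve a MUAC ≥ 125 mm and a WHZ" of at least −2; OptiMA and ComPAS have no WHZ requirement. Relapse in Table 1 is MUAC below 125.

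Strata (Randomisation): (1) MUAC below 115 mm or oedema; (2) "MUAC > 115 mm and WHZ" below −3; (3) MUAC 115 to 124 and WHZ above −3, without oedema.

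**The concern.** The primary parenthesis presents itself as a restatement of the inclusion definition but is not its complement. If malnourished means MUAC < 125 mm or WHZ < −3 or oedema, then not malnourished means MUAC ≥ 125 mm and WHZ ≥ −3 and no oedema. With strict inequalities, children on either boundary become failures.

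The boundary value is not obscure. The protocol bands MUAC in whole millimetres (115–119, 120–124), and 125 mm is the exit threshold for treatment, so readings of exactly 125 mm should not be rare.

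At stake is which children count as successes in the primary and main secondary endpoints of a trial with a 10-point non-inferiority margin. The trial is open label and the Blinding section says the data analysts know the allocation, so the choice between two readings should not be left until the data are in hand.

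**Working it through.** **Step 1: the rules applied to a MUAC of exactly 125 mm.** Other criteria are assumed met.

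| Rule | Place | Result at 125 mm |
|---|---|---|
| Malnourished by MUAC (< 125) | Eligibility criteria | No |
| Relapse by MUAC (< 125) | Table 1 | No |
| Discharge (≥ 125) | Follow-up | Yes |
| Recovered (≥ 125) | Abstract, Study outcomes, Table 2 | Yes |
| Recovered (> 125) | Table 1 | **No** |
| Favourable, by reference to the inclusion definition | Table 1 | Yes |
| Favourable, by the parenthesis (> 125) | Study outcomes | **No** |

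Only two outcome definitions put 125 mm on the failing side. WHZ of exactly −3 has the same gap in the primary outcome: inclusion needs < −3, favourable needs > −3.

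**Step 2: the plan's sample size.** Inputs from Sample size and Statistical analysis: 68% in each arm, margin 0.10, one-sided alpha 0.0125, power 90%, 5% inflation.

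n = (2.2414 + 1.2816)² × 2 × 0.68 × 0.32 / 0.10² = 12.41 × 0.4352 / 0.01 ≈ 540.1, so 541 per arm.

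Inflated: 541 / 0.95 gives 570, and 541 × 1.05 gives 569, against 568 stated. The figure reproduces to within rounding. Changing the sign alters none of its inputs.

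**Step 3: how many children might read 125 mm.** The documents give no MUAC distribution, so this is an assumption: 6-month MUAC normal, mean 127–130 mm, SD 5–8 mm, recorded to the millimetre (62–86% then read 125 mm or more). P(124.5 < X < 125.5) is:
- mean 127, SD 5: 7.4%
- mean 130, SD 8: 4.1%

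This is an upper bound on the shift in the favourable rate under that assumption, because some of these children already fail through another episode, WHZ or oedema. For illustration, if the 30% relapse rate from Sample size applied equally to them, the shift would be 0.70 × 4.1 = 2.9 to 0.70 × 7.4 = 5.2 points.

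**Step 4: effect on power if the shift is equal across arms.** Evaluable n = 568 × 0.95 ≈ 540 per arm. Power = Φ(0.10 / √(2p(1−p)/540) − 2.2414).

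| Shift (points) | Rate p | Power |
|---|---|---|
| 0 | 68% | 90.0% |
| 3 | 65% | 88.6% |
| 5 | 63% | 87.7% |
| 6 | 62% | 87.4% |

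**Step 5: an unequal shift, hypothetical only.** If the strict sign cost an intervention arm 1, 2 or 3 points more than control, power would be about 82%, 71% or 58%. Nothing in the document supplies such a difference.

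**Step 6: strata.** Two kinds of randomisable child without oedema fit none of the three: MUAC exactly 115 mm with WHZ < −3, and MUAC 115–124 mm with WHZ exactly −3. A child with WHZ exactly −3 and MUAC below 115 mm, or with oedema, is in stratum 1 and is not affected.

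**The case against.** The best defence is that the intended reading is fairly clear. The parenthesis is introduced as the inclusion definition, the abstract and Table 1 define the primary outcome by that reference alone, and eligibility, relapse, discharge and the recovery text all put 125 mm on the non-malnourished side. The two strict signs look like loose notation rather than a deliberate second endpoint. This stands as evidence of which sign to keep. It does not remove the error: the only numerical statement of the primary outcome is the strict one, and the residual clause turns every boundary child into a failure. An analysis plan not shown may settle the sign, but the definition stated here would still be wrong.

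Three stronger readings are tempting and are not supported.

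- A reader might infer that children discharged at 125 mm are then scored as primary failures. Discharge happens during outpatient treatment and the primary outcome is read at 6 months, so this ground applies only to a child measuring exactly 125 mm at that later visit. The direct clash between being discharged and not counting as recovered is with the Table 1 recovery row alone.
- A reader might infer bias against OptiMA and ComPAS because they discharge on MUAC without WHZ and their children may cluster at the threshold. That is an inference about discharge, not about 6 months, and no distribution is given. Nor are all control children held to a WHZ exit: those aged 24–59 months with moderate wasting receive no supplementation and go straight to home visits.
- A reader might infer that the strata should be rewritten. Lists were prepared in advance and enrolment was due to finish in December 2021, before the article appeared in January 2022. New wording cannot change allocations.

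**Conclusion.** The point holds as a contradiction in two endpoint definitions, established from the text without any assumption. The primary parenthesis misstates the inclusion definition at MUAC 125 mm and WHZ −3, and Table 1 and the text give different recovery rules at 125 mm.

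The size is uncertain and probably modest. A 4–7% share at exactly 125 mm depends on the assumed normal distribution and bounds the shift from above; an equal shift of 3–6 points costs about 1 to 3 points of power. The sample size is not in error on this account. A differential effect between arms cannot be excluded or demonstrated from the document. The correction is still worth making, because it decides which children count as successes in the primary and main secondary analyses.

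**What to change.** Before analysis, and without looking at results by arm:

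1. In the primary outcome, state not malnourished as MUAC ≥ 125 mm and WHZ ≥ −3 and no oedema, the exact complement of the inclusion definition.
2. Correct the recovery row of Table 1 to MUAC ≥ 125 mm, matching the abstract, the outcome text and Table 2. The non-response row, which relies on the recovery criteria, then follows.
3. Confirm and report the stratum cuts actually programmed in the randomisation software, including where children at MUAC 115 mm with WHZ < −3 and at WHZ exactly −3 were placed. Use those cuts in any stratified analysis; do not redefine the strata.

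Items 1 and 2 are wording changes to outcome definitions. They alter no treatment or discharge rule and no sample size input. Item 3 costs one query to whoever holds the randomisation program.

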**Primary**			
Favourable outcome	Composite: alive, not acutely malnourished per the definition applied at inclusion, and no additional episode of acute malnutrition throughout the 6-month observation period	Proportion	6 months post-inclusion
**Main secondary**			
Recovery	Composite: absence of bipedal oedema and a MUAC > 125 mm for two consecutive weeks, a 4-week minimum duration of RUTF treatment, and a good clinical health (without fever)	Proportion	Throughout the 6-month follow-up period
**Secondary**^a^			
Cost-effectiveness	Incremental cost-effectiveness ratio (ICER)	Ratio	Throughout the 6-month follow-up period
Consumption of RUTF per children with a favourable outcome	Sachets of RUTF consumed	Mean	6-month post-inclusion
Consumption of RUTF per recovered children	Sachets of RUTF consumed	Mean	End of RUTF treatment initiated at inclusion
Average daily weight gain in SAM children recovered	g/kg/day	Daily	End of RUTF treatment initiated at inclusion
Average daily MUAC gain in SAM children recovered	mm/day	Daily	End of RUTF treatment initiated at inclusion
Hospitalisation	Children with at least one episode of hospitalisation	Proportion	Throughout the 6-month follow-up period
Relapse to a new episode	Children with MUAC < 125 or WHZ < − 3 *Z*-score or oedema after RUTF treatment	Proportion	After recovering from the first episode of acute malnutrition
Non-response	Children who did not reach the recovery criteria	Proportion	16 weeks after inclusion
WaST	Children associated with severe and moderate stunting with acute malnutrition	Proportion	Throughout the 6-month follow-up period

^a^All the secondary outcomes will be analysed for the overall population (MUAC < 125 mm or WHZ < − 3 or oedema) and for the secondary populations (SAM WHO and MUAC < 115 mm or oedema)

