In the control arm, children included with a MUAC < 115 mm and/or WHZ < − 3 and/or nutritional oedema are treated weekly with RUTF, according to the Niger national protocol dosage table based on the child’s weight. The Niger protocol provides a RUTF daily caloric intake of 150–200 kcal/kg/day during the entire treatment schedule until recovery in children with SAM. Children under 2 years old included with a MUAC between 115 and124 mm and WHZ > − 3 without bipedal oedema are treated weekly by one sachet of RUSF per day (500 kcal/day) during the course of treatment. However, children over 2 years old meeting the same moderate anthropometric criteria are not eligible for supplementation according to the national MAM programme.

The simplified strategies apply to AM children defined as MUAC < 125 mm or bipedal oedema (+, ++) without medical complications on admission and with a good or moderate appetite test.

In contrast to the weight-based RUTF ration in the national SAM programme, the OptiMA RUTF ration is calibrated to the child’s degree of wasting based on the combination of MUAC status and weight. Thus, more nutritional support is given to the most severely malnourished children and then gradually reduced as the child’s MUAC increased. Children with MUAC < 115 mm or oedema receive 175 kcal/kg per day of RUTF. Children with MUAC 115–119 mm, either at admission or during the course of treatment, receive 125 kcal/kg per day of RUTF, and children with MUAC ≥ 120 mm receive 75 kcal/kg per day of RUTF (with a minimum of one sachet/day) until discharge from the programme.

The ComPAS strategy is the most simplified protocol, not requiring a dosage table and proposing to gradually reduce the dosage according to the child’s MUAC status only during the outpatient follow-up as follows: 2 sachets/day of RUTF to children with MUAC < 115 mm or oedema and 1 sachet/day for children in the 115–124 mm MUAC zone.

For both simplified strategies, children with oedema receive the same RUTF ration as children with MUAC < 115 mm until oedema are resolved, at which point their ration is determined by MUAC and weight.

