### Statistical analysis

All statistical analyses will be performed using the RStudio Software (Boston, MA, USA) as specified by the data analysis plan published on ClinicalTrials.gov prior to performing any analysis. Statistical tests will be carried out bilaterally with an alpha risk of 5% and unilaterally with an alpha risk of 1.25% for the non-inferiority analysis. Qualitative variables will be described in terms of numbers and percentages and provided with CIs when relevant. If necessary, comparisons of qualitative variables will be made using *χ*^2^ or Fisher exact tests. Quantitative variables will be described in terms of mean, SD, and CI or median, range, and IQR. If necessary, comparisons of quantitative variables will be made using Student’s, Wilcoxon’s, or Kruskal-Wallis tests, depending on the distribution of the variable of interest. Time delay type variables will be described in terms of the incidence of occurrence, and the probability of occurrence over time, estimated by the Kaplan-Meier method. If necessary, probability comparisons will be made using log-rank tests, or proportional risk models, after verification of the assumption of proportionality of risks.

The main analysis of the primary and secondary outcomes will be intention-to-treat and per-protocol given that this is a non-inferiority trial. Participants included in the main analyses will be described according to the diagram defined by CONSORT (Consolidated Standards of Reporting Trials) recommendations [18]. The occurrence of the primary “favourable outcome” and the secondary main outcome “recovery” will be compared between the two randomisation arms. These two comparisons will be performed both by “intention-to-treat” basis and on a “per-protocol” basis. Non-inferiority analyses will be performed on these two outcomes. Only if non-inferiority for these two outcomes is demonstrated will the other secondary analyses will be performed and, if appropriate, as a superiority analysis. Superiority will be particularly sought for cost outcomes related to RUTF cost-efficiency.

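### The two RUTF consumption outcomes average only over recovered or favourable children, so they show neither product used per child treated nor product used per success

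*Protocol article*

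**What the plan says.** Table 1 has two rows on product use: "Consumption of RUTF per children with a favourable outcome", timed at 6 months, and "Consumption of RUTF per recovered children", timed at the end of the treatment begun at inclusion. In both, the variable is "Sachets of RUTF consumed" and the aggregation is a mean; the cost-effectiveness row, by contrast, is aggregated as a ratio. No row gives sachets per randomised or per treated child.

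The table's footnote widens the scope: "All the secondary outcomes will be analysed for the overall population", as well as for the WHO-defined SAM group and the group with MUAC < 115 mm or oedema. In the overall population, control-arm children with moderate malnutrition under 2 years "are treated weekly by one sachet of RUSF per day (500 kcal/day) during the course of treatment" (Intervention section), and those over 2 years "are not eligible for supplementation according to the national MAM programme". The same children receive RUTF in the OptiMA and ComPAS arms.

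The Objectives section lists RUTF consumption among the outcomes to be compared between the three arms. The Statistical analysis section adds: "Superiority will be particularly sought for cost outcomes related to RUTF cost-efficiency". It also makes the other secondary analyses conditional on non-inferiority for the favourable outcome and for recovery.

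**The concern.** Recovery and favourable outcome are results of the allocated strategy. Averaging sachets among the children who reach them compares selected groups, and the selection may differ by arm.

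The selection also removes product that a programme has to pay for. A child who never recovers can be treated for up to 16 weeks (Table 3, footnote 1), and those sachets do not enter the recovered row. Relapse courses enter neither row: the recovered row stops at the end of the first treatment, and the favourable row excludes any child with a further episode. Yet the Sample size section assumes a relapse rate of 30%.

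The rows therefore answer how much a successful child used, not how much the strategy uses per child or per success. The second question is the one that bears on efficiency, which the Discussion section puts at the centre of the policy message.

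A different problem arises in the overall population. Supplementary product (RUSF or super cereal) given to control-arm moderate children under 2 years is not counted, so control-arm use is understated. This matters little in the two severe subgroups, where control children receive RUTF.

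**Working it through.** **No planned figure to reproduce.** The article gives no expected sachet counts. The size of the non-inferiority gate can be derived from its sample size for children with MUAC < 115 mm or oedema: 74% recovery, 10-point margin, one-sided alpha 1.25%, power 80%.

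n = 2 × 0.74 × 0.26 × (2.241 + 0.842)² / 0.10² = 366 per arm. With 5% inflation, 366 × 1.05 = 384.3, against the stated 384. The figure is reproduced.

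**Largest observed deficit that passes.** SE = √(2 × 0.74 × 0.26 / 366) = 0.0324. Half-width = 2.241 × 0.0324 = 7.3 points. Largest passing deficit = 10 − 7.3 = about 2.7 points, that is, 74% against 71.3%.

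**Hidden difference at that deficit.** Assume 122 sachets per recovered child in both arms. The Introduction gives 122 as the ComPAS average for SAM children in the cited trial; using it for recovered children is an assumption. A non-recovered child uses 112 to 224 sachets (16 weeks × 7 days at 1 to 2 per day; 224 is a ceiling).

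Sachets per recovery = 122 + [(1 − r)/r] × s

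| s | r = 74% | r = 71.3% | Ratio | Table 1 mean |
|---|---|---|---|---|
| 112 | 161.4 | 167.1 | 1.04 | 122 in both |
| 224 | 200.7 | 212.2 | 1.06 | 122 in both |

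**The ranking can reverse inside the gate.** Assume 1 sachet/day. In both arms 71.3% recover at week 6 (42 sachets). A further 2.7% recover at week 14 in arm A (98 sachets) and never in arm B. All non-recovered children use 112.

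- Table 1 mean: A = (0.713 × 42 + 0.027 × 98)/0.74 = 44.0; B = 42.0. B looks 5% cheaper.
- Per randomised child: A = 32.6 + 0.26 × 112 = 61.7; B = 29.9 + 0.287 × 112 = 62.1.
- Per recovery: A = 61.7/0.74 = 83.4; B = 62.1/0.713 = 87.1. B is 4% dearer.

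**Equal recovery, 74% in both arms.** Product used by non-recovered children, per recovery, is (0.26/0.74) × s.

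- ComPAS ration, s = 112 to 224: 39 to 79 sachets.
- Control ration of 150–200 kcal/kg/day, assumed 7 kg child, 500 kcal per sachet: s = 150 × 7/500 × 112 = 235 to 200 × 7/500 × 112 = 314, giving 83 to 110 sachets.

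None of this appears in the recovered row. Here the omission hides a saving by the simplified arm, so the bias runs the other way.

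**Counting RUTF alone, overall population.** Assume 70% of moderate children are under 2 years, a 42-day moderate course, 84 sachets per SAM child in ComPAS, and 100 or 150 in control. Figures are mean 500-kcal sachets per child.

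| Moderate share | Control, RUTF only | Control, RUTF + RUSF | ComPAS |
|---|---|---|---|
| 30% | 70.0 to 105.0 | 78.8 to 113.8 | 71.4 |
| 50% | 50.0 to 75.0 | 64.7 to 89.7 | 63.0 |
| 70% | 30.0 to 45.0 | 50.6 to 65.6 | 54.6 |

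The amount left out is share × 0.7 × 42, or 8.8 to 20.6 sachets per control child. In several cells it changes which arm uses less.

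**The case against.** The strongest objection is the gate. A reader might set the full margin against these outcomes: 74% against 64% recovery gives 200.7 against 248.0 sachets per recovery, a hidden 24%. The document does not support that size. Secondary analyses follow only after non-inferiority is shown, and a strategy truly 10 points worse than control would pass with a probability of about 1.25%. This stands and limits the size against control to the figures above. It does not remove the point, because the bias needs no recovery difference, and the gate does not directly limit OptiMA against ComPAS.

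Second, the efficiency claim may rest on the cost-effectiveness ratio, which covers the whole 6 months, and non-response, hospitalisation and relapse are reported by arm. This softens the consequence. It does not correct two outcomes that the Objectives section lists for comparison separately from cost-effectiveness.

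Third, consumption per recovered child could mean total sachets divided by the number recovered. The mean label, beside a ratio label for cost-effectiveness, points the other way, but the reading is possible; if it was meant, the table must say so. The full analysis plan is not shown and may settle it, but Table 1 does more than leave the measure open: it fixes a mean.

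Fourth, not every non-responder or defaulter is lost from the means. A child can meet the recovery criteria later, at a village visit, or be favourable at 6 months after home follow-up. The gap in the recovered row concerns children who never recover.

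Finally, a reader might take the uncounted RUSF as one more way for a failing strategy to look cheap. It is not: it makes control look cheaper and has nothing to do with non-response.

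**Conclusion.** The point holds. As worded, both rows compare subsets defined after randomisation and leave out product used without success and in relapse courses. They cannot support a statement about product per child treated or per success, and the direction of the bias is not known in advance.

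Against control, the hidden difference due to recovery alone is about 4% to 6% in sachets per recovery at the largest passing deficit (161 against 167; 201 against 212). This assumes 122 sachets per recovered child, 112 to 224 per non-recovered child and 74% recovery in control. Differences in what non-recovered children use can add more, and they remain when recovery is equal. All these sizes are illustrative.

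The RUTF-only count is a separate and smaller issue, confined in practice to the overall population, where it understates control-arm use.

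**What to change.** Replace the two rows as the compared outcomes with:

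- (a) mean RUTF sachets per randomised child over 6 months, relapse courses included;
- (b) total sachets in the arm divided by the number recovered, and by the number favourable, each with a bootstrap interval.

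Report supplementary product (RUSF or super cereal) alongside, in kcal or cost rather than added as sachets. Keep the present means as descriptive, with the denominator stated. If the existing row was already meant as (b), change the mean label to say so.

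The cost is a wording change in Table 1 and a little more analysis work. No sample size or trial procedure changes. The team should confirm that supplementary product given to control children is recorded per child, since the article does not say so.
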